### Recruitment {15}

The Austrian Health Insurance Fund will perform a FoKo database (Folgekosten database) query based on defined inclusion and exclusion criteria to identify potential participants in Lower Austria.

The FoKo database is a social insurance data warehouse that is used by all health insurance providers in Austria. FoKo combines several IT (accounting) systems of Austrian health providers in one instrument and thus enables various analyses. FoKo collects data related to medical assistance, medication, and incapacity to work as well as in-patient stays or patient transport and dental treatment. FoKo has registered approximately 1.2 million people eligible for services of the Austrian Health Insurance Fund in Lower Austria.

Based on FoKo database queries of the years 2018 and 2019, approximately 6000 potential participants will be identified. The data of the Mother-Child-Booklet, which is part of the Austrian pregnancy and childhood examinations, allows to identify pregnant women (with gestational diabetes) in order to exclude them from the study [72]. The Austrian Health Insurance Fund will contact all identified patients with type 2 diabetes mellitus by personal letter while strictly considering data privacy. Additionally, the Austrian Health Insurance Fund will inform all relevant physicians and internists in Lower Austria about the trial and ask them to inform their patients about the possibility to participate in the trial. Furthermore, the diabetes-specific self-help organizations ADA (https://aktive-diabetiker.at/) and ÖDV (https://www.diabetes.or.at/home/) will inform their members about the trial. Additionally, leaflets will be disseminated at the Customer Service Centers of the Austrian Health Insurance Fund and via the consortium member institutions’ online channels, e.g., their websites.

## Assignment of interventions: allocation

### Sequence generation {16a}

Eligible participants who have signed the informed consent will be randomized into the peer-supported IMS intervention group or the control group in a 1:1 ratio. Random assignment will be conducted using virtual urn randomization during the initial appointment.

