The intervention will be conducted twice to increase the recruitment phase. The first intervention will start in April 2022. As soon as the first cohort enters the unaccompanied phase, a second moderated cohort will start - in both cases accompanied by an equally large control group. In total, we will be in the field for 23 months. With the start of the first intervention, we will have as many intervention and control teams with 14 people each as there are registrations. With the second intervention date, the remaining persons (196 in total) form further intervention and control teams.

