Additionally, clinical visits will be designed as conveniently for the participants as possible [50, 51]. The participants will have easy access to the locations of training sessions and measurements: they can choose one out of four central locations in Lower Austria for their measurements. These locations are well known and easily accessible: the St. Pölten University of Applied Sciences and hospitals in Wr. Neustadt, Hollabrunn, and Mauer/Amstetten. These locations are equally distributed over Lower Austria from a geographical point of view and can be reached comfortably by car as well as public transport. The training sessions for the participants will take place after the first measurement at the same location. The training sessions for the moderators will be held at the St. Pölten University of Applied Sciences. Therefore, only individuals from St. Pölten or the surrounding areas are eligible to become moderators. If a participant misses one measurement, it is possible to make a new appointment within a certain timeframe.

Furthermore, study staff will call participants to schedule visits and send them reminders via SMS and e-mail 48 h before the appointment. During each measurement, participants and moderators will have the opportunity to discuss their results, such as body composition, with an experienced dietitian, which is not very common in Austria and will increase engagement [50].

Additionally, participants and moderators will receive a financial compensation of 50 EUR and a small gift after the last measurement.

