### Concealment mechanism {16b}

For the allocation of the participants, a simple urn-based randomization is carried out. For this purpose, an urn, in our case a digital card set, is filled with 196 cards. On 98 of them, it says “intervention group” and on 98 “control group.” A unique ID is assigned to each card. The participants draw the cards themselves. This gives them the feeling that they have made their own decision and makes it easier for them to accept it, even if they do not end up in the desired group.

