### Implementation {16c}

The drawing of the participants takes place during the initial appointment for the informed consent. Since the participants come continuously and from all over Lower Austria, interviews are conducted both in person and via video calls. In order to make the ballot box drawing online and offline comparable, a computer-based drawing will take place in both cases, i.e., similar to a memory game. The test persons turn over one (of 196) cards and thus find out in which group they participate and, at the same time, receive their ID for the study. The drawing takes place without putting the cards back.

The maximum group size is 14 participants. When an intervention or control group is full, the recruitment of the next group will be started. The ID numbers are therefore not consecutive within the groups, but random. There is no upper limit regarding the number of participants for the first recruitment date.

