## Trial status

This is the protocol version 6 from 21.11.2021. Recruitment has started in August 2021 and will end in September 2022.

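### The arm is drawn and shown to the participant at consent, before the T0 visit, so trial baselines are taken open-label and losses before T0 leave no T0 value

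*Protocol article*

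**What the plan says.** The protocol article fixes the moment of allocation in two places. Sequence generation {16a}: "Random assignment will be conducted using virtual urn randomization during the initial appointment". Implementation {16c}: "The drawing of the participants takes place during the initial appointment for the informed consent". The participant turns over one of 196 digital cards and will "thus find out in which group they participate"; the same card carries the study ID. The consent section {26a} allows this appointment to be held by video call or in person, and describes no measurement at it. Concealment mechanism {16b} presents the self-draw as a way to help people accept the result "even if they do not end up in the desired group".

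T0 is a different occasion. Plans for assessment {18a} describes morning group sessions in a fasting state. Intervention description {11a} puts the first measurement in a one-month phase together with the training, ahead of the seven guided months, and has people already assigned to the intervention attend training in connection with it. Section {11c} adds: "The training sessions for the participants will take place after the first measurement at the same location". Outcomes {12} first takes all outcome measures, demographics and personality traits at T0.

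The calendar comes from two statements. Trial status: "Recruitment has started in August 2021 and will end in September 2022". Section {11a}: "The first intervention will start in April 2022". The second cohort starts when the first enters its unguided phase, and each cohort is to be "in both cases accompanied by an equally large control group".

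**The concern.** A baseline should be fixed before anyone can react to the allocation. Here the participant learns the arm first and gives the baseline later, in a trial where participants cannot be blinded. Three things follow.

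- **Self-reported baselines can move with knowledge of the arm.** Quality of life, self-care, medication adherence and the extraversion score used for H5 are all first collected at T0. If such a baseline has shifted in one arm, using it as a covariate or as the starting point of change carries that shift into the group comparison.
- **HbA1c can move through behaviour.** The background section says HbA1c reflects roughly the previous 8 to 12 weeks. For anyone drawn more than 12 weeks before T0, the T0 value covers only time after the arm was known.
- **Loss between draw and T0 can depend on the arm.** The protocol itself expects some people not to get the group they hoped for. A control who leaves then is randomised but has no T0 value. Section {11b} also lets the principal investigator end participation when inclusion requirements are no longer met. A long wait after the draw turns such changes into post-randomisation exclusions.

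**Working it through.** **1. Where T0 sits.** The protocol gives a field time of 23 months. Take cohort 1 as 1 month of training and first measurement plus 7 guided months, then cohort 2 as its full 15 months (1 + 7 + 7):

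(1 + 7) + 15 = 23 months.

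This reproduces the stated figure exactly and places T0 at the start of each cohort, not at consent. Section {12} agrees: T1 is given both as 3 months after the start of the intervention and as T0 + 3 months.

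**2. The wait from draw to T0.** No draw date or T0 date is given, so these are bounds.

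- Cohort 1, earliest possible draw August 2021: T0 in March 2022 gives 7 months; T0 in April 2022 gives 8 months.
- Cohort 2, T0 about November 2022 (April 2022 + 7): a draw in April 2022 gives 7 months; a draw in September 2022 gives 2 months.

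The bounds may be off by about a month, depending on whether April 2022 is read as the training month or the first guided month. The order of draw, disclosure and T0 does not depend on them.

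**3. Is there anything earlier to fall back on?** The only pre-draw value described is the eligibility HbA1c from the most recent measurement {10}. It is not named as a baseline. The imputation in {20c} covers scales with at least 80% of items answered, so it does not replace a T0 visit that never took place.

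**4. What selective loss could do (illustration; all inputs assumed).** Suppose 10 percentage points more controls than intervention participants leave before T0, and these leavers would have had HbA1c 0.5 SD below the arm mean.

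- Shift in the remaining control mean: 0.10 × 0.5 / 0.90 = 0.056 SD.
- Planned effect: f = √(0.05/0.95) = 0.2294, so d = 2f = 0.459.
- Unadjusted: 0.056 / 0.459 = 12% of the planned effect, in favour of the intervention.
- Adjusted for T0, if the leavers' difference is stable and the T0-to-outcome correlation is r: 0.056 × (1 − r)/√(1 − r²). For r = 0.5 this is 0.032 SD (7%); for r = 0.8 it is 0.019 SD (4%).
- If the leavers had higher HbA1c instead, the sign reverses.

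**5. The urn across cohorts.** One urn of 98 + 98 cards is drawn without replacement. If cohort 1 takes 98 cards (assumed; {16c} sets no limit), the intervention count is hypergeometric:

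- SD = √(98 × 0.5 × 0.5 × 98/195) = 3.51.
- P(exactly 49:49) = 0.114; the 95% range is 42:56 to 56:42.
- Information kept at 42:56: 4 × 42 × 56 / 98² = 0.98.

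**The case against.** The sequence is stated openly and consistently, so this is a weak design choice and not a contradiction. The primary outcome is the least exposed: HbA1c is a laboratory value, measurement staff see only a code {19}, and nobody uses the app before the training held with the first measurement. Anticipation and selective loss remain as routes, and the documents show neither a size nor a direction for them. That all stands, and it limits the claim.

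Several stronger readings are tempting and are not supported:

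- **That participants did wait eight months.** Recruitment includes letters and online registration before any appointment, so the first draw may have come after August 2021.
- **That consent is mostly online.** The protocol allows both forms and gives no frequencies.
- **That early leavers have no HbA1c at all.** An eligibility value precedes the draw, although it is given no role in the analysis.
- **That intention to treat fails.** The principle is stated in {20c}. The difficulty is confined to people lost before T0, and how they are handled may properly be left to an analysis plan that is not shown.
- **That the result is biased by 12% of the planned effect.** This is one assumed scenario before baseline adjustment, and its sign could be the opposite.

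There are also practical objections to simply moving the draw. The card issues the ID that marks the T0 questionnaires, T0 is a group session with blinded staff, and small fixed blocks would make late allocations predictable in an open-label trial. These are sound, and the remedy has to respect them.

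**Conclusion.** The point holds in this form. Allocation is disclosed at consent and T0 follows at the start of the cohort. All baselines the trial collects are therefore post-allocation, open-label measurements, and people lost between draw and T0 have no T0 value. The order is stated in the text. The length of the gap, up to about 7 to 8 months in cohort 1 and roughly 2 to 7 in cohort 2, is inferred. The self-reported scales and the personality score are the most exposed; HbA1c is less so, but can still shift through behaviour or selective loss. The size and direction of any bias are unknown. Under the assumed scenario it is some 4% to 12% of the planned effect, either way.

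This is worth changing because no later analysis can recover a pre-allocation T0 measurement that was never taken. Protocol version 6 (21.11.2021) predates the first intervention, so at that version all of cohort 2 and part of cohort 1 could still be corrected.

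The urn is a minor matter. It does not guarantee the equal arms promised for each cohort, but even 42:56 costs only about 2% of the information.

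**What to change.** For everyone not yet drawn, and for all of cohort 2:

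- Issue the study ID at consent, separately from the arm card, so that T0 forms can be marked as planned.
- Make the individual computer draw after that person's T0 blood sampling and questionnaires and before the technical training, which already follows at the same site.
- Hold the draw out of sight of the blinded measurement staff and of other attendees.

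People who leave before T0 are then never randomised, and their loss cannot bias the comparison.

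For those already drawn, report losses between draw and T0 by arm, and use the pre-draw eligibility HbA1c in a sensitivity analysis where it is available.

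For the minor point, use a separate balanced card set for each cohort, without small fixed blocks, or soften the wording on equally large control groups. Include cohort in the analysis either way. If cohort 1 has already come out unequal, a balanced set for cohort 2 gives up the exact 98:98 overall, which matters little.

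Cost: a protocol amendment, a separate ID step, and attendees keeping about 2 hours free after T0 in case they draw the intervention. Messaging groups can be made up only once the T0 sessions are done. Somewhat more people must consent if 196 are to reach the draw.

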### Concealment mechanism {16b}

For the allocation of the participants, a simple urn-based randomization is carried out. For this purpose, an urn, in our case a digital card set, is filled with 196 cards. On 98 of them, it says “intervention group” and on 98 “control group.” A unique ID is assigned to each card. The participants draw the cards themselves. This gives them the feeling that they have made their own decision and makes it easier for them to accept it, even if they do not end up in the desired group.

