### Trial design {8}

The presented trial is a parallel-group, two-arm superiority RCT to evaluate the efficacy of a peer-supported IMS intervention for patients with type 2 diabetes mellitus in Lower Austria. Peer support via IMS in addition to standard therapy is compared with stand-alone standard therapy.

Moderators play a central role in peer-supported IMS intervention because they initiate and moderate the IMS exchange and discussion. They are patients with several years of disease and therapy experience because they need personal and practical experience in order to provide supportive and credible coaching. All moderators receive prior training and guiding material (see {11a}). The moderators are supported by a dietitian at regular intervals and by other study team members if needed. One moderator is responsible for one IMS group consisting of 14 participants maximum.

The participants will be fully informed about all aspects of the trial and asked to sign a consent form. The participants will be randomized at a ratio of 1:1.

The duration of the intervention is 7 months, followed by a 7-month follow-up period. The intervention will be performed twice to expand the recruitment phase. During the follow-up, the intervention group is expected to use the IMS tool without guidance by health professionals and both groups receive standard therapy.

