### Sample size {14}

An a priori calculation was performed using G-Power [68] for the primary outcome variable HbA_1c_, using an ANCOVA at 5% level of significance and 80% power. Based on previous research, we assumed a small to medium effect size for group differences in HbA_1c_ means (partial eta squared = 0.05, which corresponds to an effect size *f* = 0.229) [69–71]. Considering a 30% dropout ratio, we will include 98 randomly assigned participants in each group (196 total). The intervention group will be subdivided into seven IMS groups made up of 14 participants and one moderator each. Therefore, nine moderators (seven plus two for the compensation of possible drop-outs) will be additionally recruited (205 persons in total, 196 participants plus nine moderators). Although the moderators will participate in the assessments, their data will not be included in the analyses.

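### A single unblocked 196-card deck drawn across two cohorts does not secure the equally large control group stated for each cohort; the resulting imbalance is random and small

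*Protocol article*

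**What the plan says.** Under Concealment mechanism {16b} of the protocol article, the allocation device is one deck: "For this purpose, an urn, in our case a digital card set, is filled with 196 cards". Its composition is 98 cards per arm. Implementation {16c} adds that "The drawing takes place without putting the cards back", that participants arrive continuously and draw at the consent appointment, and that "There is no upper limit regarding the number of participants for the first recruitment date". No block and no cohort stratum is described. Trial design {8} gives the ratio: "The participants will be randomized at a ratio of 1:1".

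Intervention description {11a} sets out two cohorts, "in both cases accompanied by an equally large control group". At the first start "we will have as many intervention and control teams with 14 people each as there are registrations", and the remaining persons form teams at the second start.

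Sample size {14} says: "The intervention group will be subdivided into seven IMS groups made up of 14 participants and one moderator each". Nine moderators are recruited, two of them as spares. Trial design {8}, Intervention description {11a} and Implementation {16c} give 14 as a maximum group size.

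**The concern.** The article states a property of each cohort, namely equal arms, while its allocation procedure controls only the grand total. A deck of 98 + 98 cards is balanced for certain after card 196 and at no earlier point. Cohort 1 is formed from whoever has drawn by the first start, so its split is a chance event and cohort 2 carries the mirror image.

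The two cohorts differ in calendar time and season, and may differ in moderators. If the arms are unequally spread over them, a difference in HbA1c between cohorts enters an unadjusted comparison of arms. The same mechanism leaves the overall ratio unsecured if recruitment ends before all cards are used. It also bears on the seven full messaging groups, because two separate starts fill exactly seven groups of 14 only if the number of intervention participants in cohort 1 is a multiple of 14.

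**Working it through.** **Inputs from the article.** Deck of 196 cards, 98 per arm, no replacement (Concealment mechanism {16b}, Implementation {16c}); group size 14, seven groups (Sample size {14}); effect size f = 0.229 (Sample size {14}).

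**Assumptions.** Cohort 1 size n1 is not fixed, so a range of 56 to 140 is used. A cohort difference of 0.3 SD in HbA1c is assumed for illustration; the article gives no such figure.

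**The article's own figures.** 7 × 14 = 98, and the arms are 98:98 if every card is drawn. Both agree with the deck.

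**Balance within cohort 1.** Let k be the number of intervention cards among the first n1 draws. Then k follows a hypergeometric distribution (196 cards, 98 intervention, n1 drawn), and the gap between arms is |2k − n1|. For n1 = 98, Var(k) = 98 × ¼ × 98/195 = 12.3, so the SD of the gap is 2 × √12.3 = 7.0. The 95% range of k is 42 to 56.

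| n1 (assumed) | P(equal arms) | Mean gap | P(gap ≥ 10) | P(seven groups suffice, no hold-over) |
|---|---|---|---|---|
| 56 | 0.126 | 5.0 | 0.154 | 0.126 |
| 84 | 0.115 | 5.5 | 0.194 | 0.115 |
| 98 | 0.114 | 5.6 | 0.198 | 0.031 |
| 126 | 0.118 | 5.3 | 0.180 | 0.027 |
| 140 | 0.126 | 5.0 | 0.154 | 0.126 |

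For odd n1 exact equality is impossible.

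**Seven groups.** The last column assumes that everyone starts in the cohort in which they drew. The number of groups is then ceil(k/14) + ceil((98 − k)/14), which is seven if k is a multiple of 14 and eight otherwise. Over all n1 from 56 to 140 the chance of seven is 3 to 13%.

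**Early stop.** With 180 cards drawn in total, P(equal arms) = 0.205 and the mean gap is 3.0 persons.

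**Consequence for the analysis.**
- Precision at a 42:56 split: variance ratio (1/42 + 1/56)/(2/49) = 0.04167/0.04082 = 1.02, a loss of about 2%.
- Shift of an unadjusted contrast: (gap/98) × 0.3 SD. At 42:56 this is 14/98 × 0.3 = 0.043 SD; at the typical gap it is 5.6/98 × 0.3 = 0.017 SD.
- Against the planned effect d = 2f = 2 × 0.229 = 0.458, these are 0.043/0.458 = 9% and 0.017/0.458 = 4%.

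**The case against.** The strongest reply is that cohorts are formed by teams, not by date of drawing. Intervention description {11a} speaks of teams of 14 and of remaining persons who join the second start, and Implementation {16c} opens the next group when one is full. Control participants need no chat group, so sorting them into teams makes most sense as a way of matching cohort sizes. If only matched full teams start and the surplus waits, both stated properties can hold once all 196 cards are drawn.

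Part of this stands. A reader might infer that the plan cannot deliver seven groups of 14. The documents do not support that: the deck holds exactly 7 × 14 intervention cards, seven full groups are reachable if surplus people are held over, groups below 14 are allowed, and an eighth group could be covered from the two spare moderators.

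For equal arms, however, the reply needs a rule that the article does not state. Starting every full team is not enough. The chance that cohort 1 has as many full intervention teams as full control teams is 94% for n1 = 98, but 56% for 60, 11% for 84 and 13% for 56 or 140. Matched teams would have to be imposed. People who already know their arm would then wait for the second start, which comes only after the first cohort's seven guided months.

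Two further points against the concern also stand. The article lists no covariates for its repeated measures ANCOVA; a cohort term may well be in an analysis plan that is not shown, so its absence is not a fault. And the 0.04 SD shift combines the edge of the 95% range with an assumed cohort effect and no adjustment; the typical figure is about 0.02 SD.

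**Conclusion.** The statement of equal arms in each cohort is not secured by the allocation procedure as described. For assumed cohort 1 sizes of 56 to 140, exact equality has a chance of about 11 to 13% at even sizes, with a typical gap of 5 to 6 persons. Seven full groups are conditional: 3 to 13% if everyone starts where they drew, reachable with hold-over.

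A reader might go further and infer that arm and cohort are confounded so as to bias the result, or that the 1:1 ratio breaks down if recruitment falls short. Neither follows. The randomization is valid, the imbalance is symmetric around zero, and a stop at 180 leaves a mean gap of about 3. The cost is about 2% in precision at 42:56 and, under the assumed 0.3 SD cohort difference, a typical shift of about 0.02 SD (0.04 SD at 42:56). The point is worth correcting because the article promises something that its procedure does not deliver and because the correction is nearly free, not because the primary result is at risk.

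**What to change.** 1. Include cohort as a fixed factor in the primary HbA1c model. This costs one model term and has no practical downside.
2. For cards not yet drawn, do one of the following.
   - Balance by cohort, for example with consecutive decks of 28 cards (14 per arm), and close cohort 1 at the end of a deck. Used from the first card, seven such decks give equal arms in each cohort and, if all are used up, seven groups of 14. The price is predictability. For someone who tracks the draws, the expected number of correct guesses above half is (4^m/C(2m,m) − 1)/2 for m cards per arm: 8.3 for the single deck (m = 98), against 7 × 2.85 = 19.9 of 196 for seven decks (m = 14). Trial status says that recruitment began in August 2021, so any change can apply only to undrawn cards, which need not divide evenly between the arms.
   - Or keep the deck and delete the equal-size statement in Intervention description {11a}. This costs an edit.
3. State in Implementation {16c} whether people beyond a full team start at once in a smaller group or wait for the second start. This costs a sentence.
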